### Sample size and power calculation

The statistical considerations for this study are largely based on a previous study conducted at Virginia Commonwealth University (VCU) on 24 lung cancer patients [23, 29]. Prior to this multi-institutional clinical trial, the VCU study was the largest AV biofeedback investigation, recruiting a total of 26 lung cancer patients, however, 2 patients dropped out due to not being treated with radiotherapy or rapid worsening of disease, and so their data was not collected. In the VCU study 109 breathing sessions were performed comparing AV biofeedback to free breathing, of which, 87 sessions (80 %) demonstrated more regular breathing with AV biofeedback. Framing this is in a more clinical relevant way: irregular breathing motion exacerbates the systematic errors (Σ) arising from motion image artefacts and variations between the planned and treated anatomy, as well as random errors (σ) from day-to-day variations in the treated anatomy [30, 15, 31]. To combine systematic and random errors and estimate the margin contribution due to breathing irregularity we will use the van Herk method [32]: margin = 2.5Σ + 0.7σ, incorporating the respiratory components of systematic and random errors. A clinically significant difference in clinical improvement due to AV biofeedback has been determined to be a margin calculation of less than 5 mm. This magnitude of reduction was elected as clinically significant because this is the same magnitude of displacement attributed to contributing to significant artefacts and errors during radiotherapy procedures as detailed in AAPM Task Group 76 [4]. From this van Herk calculation, in the VCU study there were 14/24 patients with margins <5 mm with AV biofeedback, while only 5/24 for free breathing.

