In this proposed study, to get a more accurate indication of the proportion of patients with reduced margins calculated using the van Herk method we have designed an exploratory phase II randomised study examining the potential impact of an AV biofeedback system in regulating breathing in patients receiving radiation therapy for the treatment of lung cancer. Without the AV biofeedback system, it is conservatively estimated that approximately 40 % of patients naturally exhibit regular breathing (margin component below 5 mm). Increasing this proportion to 60 % using the AV biofeedback system would be clinically worthwhile. Based on Simon’s design, [33] a sample size of 50 patients receiving the AV biofeedback system will have at least 80 % power with 95 % confidence to rule out a regular rate of 40 % in favour of a 60 % rate. To minimise patient selection bias and provide an estimate of regular breathing from a contemporary control, the proposed design will be a randomised phase II with a 50 patients receiving the intervention and 25 receiving current standard of care. Patients will be randomised in a 2:1 ratio, with 2/3 of the patients being recruited into the AV biofeedback (intervention) arm and 1/3 in the free breathing (control) arm as illustrated by Fig. 3. 2:1 randomisation is appropriate as within the interventional arm there is a screening procedure where only patients whose breathing is more regular with AV biofeedback use this system for their imaging and treatment procedures. Patients will be stratified by treating institution and for treatment intent (palliative vs. radical) to ensure similar balance in the arms across the sites. As the study is not powered for formal comparisons between the groups, estimates of the proportion of patients which do not experience irregular breathing will provide information as to whether further investigation is warranted.

Assuming a contamination and dropout rate of no more than 10 %, this study will require that 75 + 8 = 83 patients be recruited (the 10 % value was based on the 2/26 patient drop-out rate in the VCU study).

Patients at each institution will be treated per department protocol with no additional constraints on dose, fractionation, immobilisation or image guided procedures. Results will be adjusted for institution (using a fixed effect) to account for differences between institutions.

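### The go-further judgement and the sample size use the yes/no margin (<5 mm), while the primary-objective metrics are continuous and not linked to it; a continuous between-arm estimate should be named alongside

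*Protocol article*

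**What the plan says.** In the Protocol article, Sample size and power calculation, the margin is continuous to begin with: "To combine systematic and random errors and estimate the margin contribution due to breathing irregularity we will use the van Herk method", with margin = 2.5Σ + 0.7σ in millimetres. It is then cut at 5 mm, and a patient below the cut counts as breathing regularly. The sample size rests on that yes/no result. Fifty patients receiving AV biofeedback "will have at least 80 % power with 95 % confidence" to "rule out a regular rate of 40 % in favour of a 60 % rate".

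The same section adds 25 controls to give a contemporary estimate and limits what the two arms can show: "As the study is not powered for formal comparisons between the groups". That sentence continues with the basis for going further: "estimates of the proportion of patients which do not experience irregular breathing will provide information as to whether further investigation is warranted". The Discussion repeats the proportion as that basis.

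The Data analysis section uses other quantities for the primary objective: RMSE in displacement, RMSE in period, and an artefact measure built on the normalised correlation coefficient (NCC) between adjacent edge slices. No sentence connects these, or the margin in millimetres, to the judgement on further investigation.

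On adjustment, the sample size section names institution as a fixed effect. The Patient randomisation section lists two minimisation factors, institution and treatment intent.

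**The concern.** Regular breathing means a margin on one side of 5 mm in the sample size section and a continuous RMSE in the Data analysis section. Only the first is tied to whether the work goes on. Cutting a continuous measure at one value loses information: margins of 6 mm and 12 mm count the same, while 4.9 mm and 5.1 mm count as opposites.

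The loss matters most for the randomised contrast, which has only 25 controls. That contrast is the safeguard against a wrong benchmark. The 40% reference rate is an assumption, and the one free-breathing rate in the article is 5/24 = 21%. If the reference is uncertain, the comparison with concurrent controls should be read on a scale that uses the data well.

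**Working it through.** **Inputs.** From Sample size and power calculation: p0 = 0.40, p1 = 0.60, 50 intervention and 25 control patients, and earlier-study rates of 14/24 = 0.583 with AV biofeedback and 5/24 = 0.208 with free breathing. The article gives no SD or distribution for margin or RMSE.

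**1. The plan's own figure.** Exact binomial, n = 50, one-sided 0.05 (sidedness is not stated; this reading fits):
- Smallest r with P(X ≥ r | 0.40) ≤ 0.05 is r = 27, with actual alpha 0.031.
- P(X ≥ 27 | 0.60) = 0.844.

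This meets the stated minimum of 80%, so the figure reproduces.

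**2. Between-arm precision on the proportion.**
- SE = √(0.24/50 + 0.24/25) = √0.0144 = 0.12.
- 95% CI half-width = 1.96 × 0.12 = 0.235, about 24 percentage points. The target difference is 20 points.

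**3. Between-arm power on the proportion, two-sided 5%.**
- Normal approximation: pooled p = (50 × 0.6 + 25 × 0.4)/75 = 0.533; SE under the null = √(0.533 × 0.467 × (1/50 + 1/25)) = 0.122. Power = Φ[(0.20 − 1.96 × 0.122)/0.12] = 37%.
- Chi-square test: 41%. Fisher's exact test: 34%.

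**4. The same contrast on the continuous scale.** Assumption: the margin, or its log, is normal with equal SD in both arms.
- 60% against 40% below one cut-off is a shift of d = z(0.6) − z(0.4) = 0.253 + 0.253 = 0.507 SD.
- Non-centrality = 0.507 × √(50 × 25/75) = 0.507 × 4.082 = 2.07.
- Power from the noncentral t with 73 df = 53% (normal approximation 54%).
- 95% CI half-width = 1.96 × √(1/50 + 1/25) = 0.48 SD, just inside the 0.507 SD target.

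**5. Sample size equivalent.** For 80% power, two-sided, 2:1:
- Proportion: 73 + 146 = 219.
- Continuous: 46 + 92 = 138.
- Ratio: 138/219 = 0.63.

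**6. Range over assumptions.**

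| Scenario (50 vs 25, two-sided 5%) | Proportion | Continuous |
|---|---|---|
| 60% vs 40%, uniform shift | 34–41% | 53% |
| 60% vs 40% overall, 20–40% of the AV arm with no shift | about 41% | about 52% |
| Earlier-study rates, 58.3% vs 20.8% (d = 1.02 SD) | 90% | 99% |

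The second row reflects the design: patients in the intervention arm who breathe more regularly without guidance are treated without it but stay in that arm. The third row uses the normal approximation.

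**7. Adjustment.** Minimisation uses institution and treatment intent; the stated adjustment covers institution only.

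**The case against.** The strongest answer is that the plan does not do what a quick reading suggests. A reader might infer that the decision rests solely on the yes/no margin and that the continuous data are thrown away. The article does not support that. RMSE and the NCC-based measure are planned metrics of the primary objective, and the proportion is said only to inform the judgement. A reader might also infer that the sample size is wrong or that a planned between-arm test falls short of its power. Neither holds: the single-arm figure reproduces, and the sample size section disclaims powered comparisons between the groups.

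Three further points carry weight:
- **The cut-off is reasoned.** The article ties 5 mm to a displacement linked with significant artefacts and errors, and a responder proportion is an ordinary phase II endpoint. A difference in mean log margin has no stated clinically relevant size here. So the proportion should stay as the clinical summary.
- **The gain depends on a model that the article cannot confirm.** This stands, since no SD is given. The particular worry that the intervention arm mixes guided and unguided patients does not remove the gain, as the second row of the table shows. At the earlier study's larger effect both analyses are well powered and the gap is small.
- **Model details belong in an analysis plan that is not shown.** That is fair for transformations and covariate coding, and their absence is not raised here. The point is narrower: the article itself fixes what will inform the next step, and it names only the proportion.

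**Conclusion.** The point holds as a cheap improvement and not as an error in the plan. The sample size and the only stated basis for going further use the dichotomised margin, while the continuous primary-objective metrics are left unconnected to that judgement. At the planned rates, two-sided between-arm power is about 34–41% on the proportion and about 52–53% on the continuous margin. At the earlier study's rates the figures are 90% and 99%.

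These sizes rest on an approximately normal (log) margin with equal SDs, relaxed only for a share of the AV arm with no shift. The continuous analysis does not rescue the comparison: it stays below 80% at 60% against 40%, so it remains an estimate with an interval and not a powered test.

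**What to change.** Keep the proportion below 5 mm and the single-arm test against 40% as they are. Alongside them, name a between-arm difference in mean log margin, and likewise in log RMSE in displacement, with a 95% CI. Back-transformed, each is a ratio of geometric means. Adjust for institution, as already planned, and also for treatment intent. State that this estimate and the proportion will be read together when judging whether further investigation is warranted.

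The cost is one extra model per measure on data already held, with no added patients or measurements and no planned analysis removed. The downside is a distributional assumption; a rank-based comparison as a sensitivity check covers it.

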## Abstract

**Background:**

There is a clear link between irregular breathing and errors in medical imaging and radiation treatment. The audiovisual biofeedback system is an advanced form of respiratory guidance that has previously demonstrated to facilitate regular patient breathing. The clinical benefits of audiovisual biofeedback will be investigated in an upcoming multi-institutional, randomised, and stratified clinical trial recruiting a total of 75 lung cancer patients undergoing radiation therapy.

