**Methods/Design:**

To comprehensively perform a clinical evaluation of the audiovisual biofeedback system, a multi-institutional study will be performed. Our methodological framework will be based on the widely used Technology Acceptance Model, which gives qualitative scales for two specific variables, perceived usefulness and perceived ease of use, which are fundamental determinants for user acceptance. A total of 75 lung cancer patients will be recruited across seven radiation oncology departments across Australia. Patients will be randomised in a 2:1 ratio, with 2/3 of the patients being recruited into the intervention arm and 1/3 in the control arm. 2:1 randomisation is appropriate as within the interventional arm there is a screening procedure where only patients whose breathing is more regular with audiovisual biofeedback will continue to use this system for their imaging and treatment procedures. Patients within the intervention arm whose free breathing is more regular than audiovisual biofeedback in the screen procedure will remain in the intervention arm of the study but their imaging and treatment procedures will be performed without audiovisual biofeedback. Patients will also be stratified by treating institution and for treatment intent (palliative vs. radical) to ensure similar balance in the arms across the sites. Patients and hospital staff operating the audiovisual biofeedback system will complete questionnaires to assess their experience with audiovisual biofeedback. The objectives of this clinical trial is to assess the impact of audiovisual biofeedback on breathing motion, the patient experience and clinical confidence in the system, clinical workflow, treatment margins, and toxicity outcomes.

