## Methods/Design

This study aims to assess the clinical impact of AV biofeedback by recruiting 75 lung cancer patients across seven radiation oncology departments. What follows is an outline of the AV biofeedback setup, primary and secondary objectives, participant selection criteria, the study workflow, and statistical considerations for our study design.

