### Objectives

This clinical trial will recruit 75 lung cancer patients across 7 radiation oncology departments testing the following objectives:

Primary objective: In a prospective multi-institutional randomised clinical trial we will test the hypothesis that AV biofeedback will significantly improve breathing regularity and reduce medical imaging errors for lung cancer patients undergoing imaging and treatment procedures during radiotherapy.

Secondary objectives will involve patient-specific and department-specific objectives:

Patient-specific objectives are to evaluate the impact of AV biofeedback by:Quantifying the proportion of patients for whom breathing is more regular with AV biofeedback,Quantifying the variability in breathing motion throughout a course of treatment,Quantifying the improvement in image quality with AV biofeedback,Evaluating the patient experience through a perception of care survey,Developing indications and contra-indications for the use of AV biofeedback,Quantifying the differences in image-guided radiotherapy (IGRT) shifts during treatment, andRecording toxicity outcomes for up to 12 months after treatment has been completed.

Department-specific objectives are to evaluate the impact of AV biofeedback on clinical testing by:Quantifying any practice changes (e.g. margin reduction),Quantifying the impact on workflow using the AV biofeedback device through time-motion studies,Evaluating the operator and clinician confidence in the AV biofeedback device’s reliability and clinical efficacy through a technology-impact survey,Quantifying the system robustness through hardware and software fault reporting, andPerforming system quality assurance, sharing the results through web-based uploads and provide feedback for QA improvement.Our methodological framework will be based on the widely used Technology Acceptance Model (TAM) [25, 26]. The TAM gives qualitative scales for two specific variables, perceived usefulness and perceived ease of use, which are fundamental determinants for user acceptance.

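### The number to recruit is given as 75 in four places and as 83 in the sample-size section; 75 leaves out the plan's own allowance for loss

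*Protocol article*

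**What the plan says.** Four places in the protocol article give 75 as the number to recruit:

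- Abstract, Background: "recruiting a total of 75 lung cancer patients undergoing radiation therapy".
- Abstract, Methods/Design: "A total of 75 lung cancer patients will be recruited across seven radiation oncology departments across Australia".
- Methods/Design, opening paragraph: "by recruiting 75 lung cancer patients across seven radiation oncology departments".
- Objectives: "This clinical trial will recruit 75 lung cancer patients across 7 radiation oncology departments".

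The section Sample size and power calculation gives a different figure. It first sets the arm sizes: "the proposed design will be a randomised phase II with a 50 patients receiving the intervention and 25 receiving current standard of care". It then makes an allowance, "Assuming a contamination and dropout rate of no more than 10" per cent, and concludes that "this study will require that 75 + 8 = 83 patients be recruited". It explains that "the 10 % value was based on the 2/26 patient drop-out rate in the VCU study".

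The figure 83 appears only there. Nowhere is 75 described as the number left after loss, or as the number to be analysed.

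**The concern.** All five statements speak of recruiting, so they cannot all be read as describing the same quantity. On the sample-size section's own derivation, 75 is the number needed before any allowance for loss and 83 is the number to enrol. A site or a reader who takes the Objectives at face value would regard recruitment as complete at 75. One who takes the sample-size section would regard it as complete at 83. Each could claim to be following the protocol.

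At stake is whether the trial ends with the 50 and 25 patients it planned on. The intervention arm of 50 carries the only power statement in the article. The control arm of 25 is there to give a contemporary estimate of regular breathing, and at that size it is already imprecise.

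**Working it through.** **Inputs, all from Sample size and power calculation.** Arms 50 + 25 = 75; loss no more than 10%; source rate 2/26 = 7.7%; allocation 2:1; rates 40% (to be ruled out) and 60%; at least 80% power with 95% confidence. The article does not say whether the 95% is one- or two-sided, and it states no cut-off.

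**1. Reproduce the stated target.** 75 × 1.10 = 82.5, rounded up to 83. This matches the article's 75 + 8.

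**2. Does 83 protect 75?** Ten per cent of 83 is 8.3. Patients are whole, so a loss within the ceiling is at most 8, and 83 − 8 = 75. Losing 9 would be 9/83 = 10.8%, above the ceiling. If the ceiling also held in each arm, a 55:28 split would lose at most 5 and 2, leaving 50 and 26. At the source rate, 83 × 24/26 = 76.6 remain. The alternative convention divides by the retained fraction: 75/0.90 = 83.3, rounded up to 84. If 10% is read as an expected rate instead of a ceiling, 83 × 0.90 = 74.7 remain on average, and 84 × 0.90 = 75.6.

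**3. What remains if only 75 are recruited?**

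- Full 10% lost: 75 × 0.90 = 67.5. By arm, 50 × 0.90 = 45 and 25 × 0.90 = 22.5.
- Source rate lost: 75 × 24/26 = 69.2, of whom 50 × 24/26 = 46.2 are in the intervention arm.

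At the ceiling the shortfall is 75 − 67.5 = 7.5 patients. The gap between the two targets is 8 patients, or 8/75 = 10.7% of the smaller one.

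**4. Does the stated power survive?** Exact binomial, single arm. For each n the cut-off is the smallest number of successes with one-sided error of at most 0.05 at a true rate of 40%; power is taken at 60%.

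| Intervention patients | Cut-off | One-sided error | Power |
|---|---|---|---|
| 50 | ≥ 27 | 0.031 | 0.844 |
| 46 | ≥ 25 | 0.034 | 0.825 |
| 45 | ≥ 24 | 0.048 | 0.856 |

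The row for 50 reproduces the article's claim of at least 80%. At a one-sided level of 0.025, 50 patients (cut-off 28) give only 0.766, so the claim fits the one-sided 5% reading. Power at 45 is slightly higher than at 50 because the test is discrete: at 45 the attained error lies closer to 0.05.

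**5. Effect on precision.** Approximate 95% half-width = 1.96 × √(p(1 − p)/n).

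- Control, p = 0.40: n = 25 gives 1.96 × √(0.24/25) = 0.192; n = 22 gives 1.96 × √(0.24/22) = 0.205.
- Intervention, p = 0.60: n = 50 gives 1.96 × √(0.24/50) = 0.136; n = 45 gives 1.96 × √(0.24/45) = 0.143.

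Each interval widens by about one percentage point on either side.

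**The case against.** The best defence is that the allowance is not missing from the plan. The section that sets the sample size states 83, shows the sum and gives the source of the rate. The other four statements can be taken as shorthand for the 50 + 25 design, and nothing says the trial will close at 75. It can be added that 67 to 68 is close to a worst case: 10% is a ceiling, it covers contamination as well as dropout, and the article does not say that contaminated patients are left out of the analysis. The trial is also described as exploratory and not powered to compare the arms.

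Most of this stands, and it limits the consequence. It does not remove the contradiction, because the shorthand statements, the Objectives among them, say that 75 is the number recruited. Nor is this a matter of a journal article leaving detail out: both figures are printed, and they disagree.

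Three stronger readings may tempt a reader, and the document supports none of them.

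- *The 83 is an arithmetic error and should be 84.* The assumed loss is a ceiling, and under that ceiling 83 leaves 75 whole patients. Dividing by 0.90 is another convention and changes the total by one patient. An exact 56:28 split is no strong argument either, since allocation is by minimisation.
- *Stopping at 75 would cost the trial its power.* The only power statement concerns the intervention arm, and it is still met at 45. The article states no precision figure that could be breached.
- *Only about 36 patients would actually use the device (80% of 45).* The 80% is 87 of 109 breathing sessions in the previous study, not a proportion of patients. Patients screened off the device stay in the intervention arm. That question is separate and arises equally at 83.

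**Conclusion.** The recruitment target is internally inconsistent: 75 in four places, 83 in one, with no reconciling sentence. By the article's own derivation 83 is the number to recruit and 75 the number wanted after loss, so recruiting to 75 would omit the allowance.

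The size is modest. At worst within the stated ceiling, about 67 to 68 patients would remain (about 45 and 22 to 23) in place of 75 (50 and 25). The stated power would still hold and the intervals would be slightly wider. This assumes that the whole 10% is lost to analysis, that loss is spread evenly over the arms, that 95% confidence means a one-sided 5% test, and that the cut-off is set for the number actually available.

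It is worth correcting because the figure tells seven departments when to stop, and because the repair costs almost nothing. It does not show that the sample size is inadequate.

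**What to change.** State 83 as the number to recruit in both places in the abstract, in the opening of Methods/Design and in the Objectives. Wherever 75 is kept, label it as the evaluable number, 50 intervention and 25 control. One sentence in the sample-size section can link the two figures.

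The cost is wording only; no patient is added beyond the 83 already planned. If the sponsor prefers to treat 10% as an expected rate and divide by 0.90, the target becomes 84, at a cost of one more patient. That is a choice, not a necessary correction.

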### Patient randomisation

This trial is stratified, hence, study group random allocation will be determined by minimisation [27, 28]. Patients will be stratified by treating institution and for treatment intent (palliative vs. radical) and minimisation considerably reduces the imbalance of these stratification factors across the control and intervention groups of the study. Patients will be randomised in a 2:1 ratio, 2 out of 3 patients will be randomised into the AV biofeedback (intervention) arm and 1 out of 3 will be randomised into the free breathing (control) arm as illustrated by Fig. 3.

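### Allocation is minimised on institution and treatment intent, but the stated adjustment names institution alone; if intent is prognostic, between-arm standard errors will be reported somewhat too large

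*Protocol article*

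**What the plan says.** The Patient randomisation section of the protocol article fixes the allocation method: "This trial is stratified, hence, study group random allocation will be determined by minimisation". It then names the factors: "Patients will be stratified by treating institution and for treatment intent (palliative vs. radical) and minimisation considerably reduces the imbalance of these stratification factors". The Abstract, the Sample size and power calculation section and the Discussion name the same two factors.

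The only covariate adjustment in the article is the last sentence of Sample size and power calculation: "Results will be adjusted for institution (using a fixed effect) to account for differences between institutions". It directly follows a statement that each department treats by its own protocol. Treatment intent is not mentioned as a term in any analysis.

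The design has seven departments, and on arm sizes the article says "the proposed design will be a randomised phase II with a 50 patients receiving the intervention and 25 receiving current standard of care". The power statement is a one-sample test of a 40% against a 60% rate of regular breathing in the 50 intervention patients. The same section says the study is not powered to compare groups. The primary objective nevertheless states a hypothesis of significant improvement, to be tested in a randomised trial.

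**The concern.** Minimisation makes the arms alike on intent, so chance imbalance in intent contributes almost nothing to the true variability of the treatment estimate. The usual model-based standard error does not know this. If intent is left out, its contribution to the outcome stays in the residual variance, and the standard error is computed as though intent had been left to chance. The standard remedy is to put every balancing factor in the model. Here the stated adjustment takes up one of the two.

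What is at stake is the width of between-arm confidence intervals and the power of between-arm tests. With 25 controls that precision is already low, and these estimates are meant to inform whether further study is warranted.

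**Working it through.** **Inputs from the article.** 75 patients, 50 and 25 by arm; 7 institutions; 2:1 minimisation on institution and intent; design rates 40% and 60%.

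**Inputs assumed, because the article does not give them.** The share of patients in one intent category, π (0.3 or 0.5), and the effect of intent on the outcome: d residual SDs for a continuous outcome, or b as a difference in proportions for a binary one.

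**1. The plan's own figure.** Exact binomial, n = 50, success declared at 27 or more: one-sided α = 0.0314 under 40%, power = 0.844 under 60%. The claim of at least 80% power with 95% confidence therefore reproduces as a one-sided statement. At one-sided 0.025 the cut-off is 28 and power is 0.766. No between-arm model enters this calculation, so intent cannot affect it.

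**2. Continuous outcome, by formula.** With residual SD 1, the standard error of the arm difference is about √(1/50 + 1/25) = √0.06 = 0.245. Omitting a balanced binary factor raises the residual variance from 1 to 1 + π(1−π)d², so

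SE without intent / SE with intent ≈ √(1 + π(1−π)d²).

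- π = 0.5: d = 0.3 gives √1.0225 = 1.011; d = 0.5 gives √1.0625 = 1.031; d = 1 gives √1.25 = 1.118.
- π = 0.3: d = 0.3 gives √1.0189 = 1.009; d = 0.5 gives √1.0525 = 1.026; d = 1 gives √1.21 = 1.100.

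**3. Continuous outcome, by simulation.** 4,000 trials per setting, minimisation with a random element, linear model with fixed site effects, no treatment effect, two-sided 5% test:

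| π | d | Reported SE, intent omitted | True sampling SD, intent omitted | Reported SE, intent included | Ratio of reported SEs | Rejection, omitted | Rejection, included |
|---|---|---|---|---|---|---|---|
| 0.3 | 0 | 0.246 | 0.249 | 0.246 | 1.000 | 4.8% | 4.7% |
| 0.3 | 0.3 | 0.249 | 0.245 | 0.246 | 1.009 | 4.0% | 4.3% |
| 0.3 | 0.5 | 0.253 | 0.247 | 0.247 | 1.025 | 4.2% | 4.6% |
| 0.3 | 1.0 | 0.272 | 0.249 | 0.247 | 1.101 | 3.2% | 5.0% |
| 0.5 | 0.3 | 0.249 | 0.251 | 0.246 | 1.011 | 5.2% | 5.5% |
| 0.5 | 0.5 | 0.253 | 0.244 | 0.246 | 1.029 | 3.8% | 4.4% |
| 0.5 | 1.0 | 0.275 | 0.256 | 0.246 | 1.118 | 3.5% | 5.8% |

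The ratios match the formula. The Monte Carlo error of a 5% rejection rate is √(0.05 × 0.95/4000) = 0.34 points. Mean bias in the treatment estimate without intent was about zero (at most 0.007 in size in any setting run).

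The true sampling SD hardly moves when intent is added at d = 1: from 0.249 to 0.247 at π = 0.3, and from 0.256 to 0.254 at π = 0.5. What changes is the standard error reported.

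**4. Binary outcome, risk difference.** With a 40% rate in both arms and π = 0.5, the total variance is 0.4 × 0.6 = 0.24, of which intent explains 0.25b². The ratio is √(0.24/(0.24 − 0.25b²)):

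- b = 0.10: √(0.24/0.2375) = 1.005 (simulated 1.005)
- b = 0.20: √(0.24/0.23) = 1.022 (simulated 1.022)
- b = 0.30: √(0.24/0.2175) = 1.050 (simulated 1.051)

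At b = 0.30, simulated between-arm power for 40% against 60% goes from 37.4% without intent to 41.1% with it.

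**5. Binary outcome, logistic model** (no site term, 3,000 trials per setting). At b = 0.40, omitting intent gives a mean SE of 0.498 against a sampling SD of 0.459, with 2.6% rejection. Including it gives 0.553 against 0.562, with 4.7% rejection. The adjusted SE is numerically larger because the odds ratio being estimated is a different one, but the unadjusted test is still the conservative one.

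**The case against.** The strongest reply is that the adjustment sentence is not a covariate list. It does not say that institution is the sole covariate, its stated purpose is to handle differences between sites, and it sits beside the remark on departmental practice. The article is condensed, and an analysis plan that is not shown may include intent. This stands in part: a reader might infer that the plan has decided to exclude intent, and the text does not say so. What remains is that the article does state an adjustment, and it names one of its two balancing factors.

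Second, nothing in the article links palliative or radical intent to breathing regularity, image artefacts or the 5 mm margin criterion. This stands. The size is conditional, and a 1 SD effect is a large assumption.

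Third, the calculation that sets the sample size is one-sample, and the study is described as exploratory and not powered to compare groups. This also stands and limits the weight of the point. It does not remove it, because the primary objective is framed as a hypothesis test in a randomised trial and the article itself says that results will be adjusted.

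**Conclusion.** The mismatch is in the text and its direction is settled: if intent is prognostic, omitting it makes reported between-arm standard errors too large and the tests conservative. The size runs from nothing to about 10-12% for a continuous outcome, and is about 0.5-5% for a risk difference over intent effects of 10 to 30 points. These figures rest on the assumed intent effects and on a 30% or 50% intent split for the continuous outcome (50% in the risk-difference formula).

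Three stronger readings are tempting and not supported. A reader might infer a biased treatment estimate or too many false positives; the simulations show bias near zero and, where intent matters appreciably, rejection below 5%. A reader might infer that the trial's actual precision is wasted; in the linear model the true sampling SD is almost the same either way, and the loss is in reported precision and in power. A reader might infer that the sample size is undermined; the 50-patient calculation does not depend on this. It is a minor point, worth correcting because the correction is almost free.

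**What to change.** Replace the adjustment sentence with: *Between-arm results will be adjusted for both minimisation factors, institution and treatment intent (palliative vs. radical).*

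The cost is one sentence and one degree of freedom: a linear model with arm and seven site terms on 75 patients leaves 75 − 8 = 67 residual degrees of freedom, and adding intent leaves 66. The variable is already recorded for allocation. The sample size, the one-sample test and patient management do not change.
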